2.3 Clinical significance of proposed protocol

A major proportion of morbidity and mortality in term neonates is due to respiratory disorders characterized by abnormal gas exchange and elevated A-a DO2. Simple non-invasive techniques of NO administration may decrease the need for mechanical ventilation and subsequent need for ECMO in this population. This improved short-term outcome may result in a lower mortality, earlier discharge and both direct and indirect cost savings. None of the studies to date have so far evaluated NO administration by oxygen hood in the neonatal population, though NO administration during mechanical ventilation has been shown to be effective and preliminary data on alternative methods of administration such as by nasal and nasopharyngeal cannulae have been shown to be feasible. Therefore, this protocol has been designed as a pilot trial with sufficient power to evaluate the physiologic efficacy of inhaled NO in improving oxygenation in neonates with markedly elevated A-a DO2 gradients.

**3. Experimental design and methods**

3.1 Design

This clinical trial will be a randomized and placebo-controlled crossover single center study.

3.2 Entry and exclusion criteria

*Entry criteria:*

1. Gestational Age >34 completed weeks (>35)

2. Age < 48 hrs

3. A-a DO2 >500, <600, on two post-ductal arterial blood gases one hour apart, while on 100% O2 by oxygen hood

1. Post-ductal arterial access (UAC or posterior tibial or dorsalis pedis arterial line)
2. Admitted to UAB Regional NICU (Inborn or Outborn)

*Exclusion criteria:*

### 1. Cardiac disease (structural disease with right to left or mixing lesions), not including patent ductus arteriosus (PDA) or patent foramen ovale (PFO)

2. Rapid deterioration requiring mechanical ventilation before entry into the study

3. Major malformations

4. Major neurologic or metabolic disorder or other illness leading to hypoventilation and hypercarbia

3.3 Randomization procedure

Following informed consent from the parent/guardian, the infants will be randomly assigned to the NO group or control (oxygen) group by the study coordinator using blocks of sealed envelopes. The allocation proportions for the NO and control group will be 1: 1.

3.4 Apparatus, protocols, and monitoring

Apparatus:

We have developed a "double-hood" model for the administration of NO via oxygen hood. The oxygen/NO/N2 blend is administered to inner hood and
suctioned out of outer hood (and inner hood via NO/NO2 sensors). The inner hood is made of Plexiglas (Olympic oxyhood; 10 inch diameter) and the outer hood is made of plastic sheeting (NOVA tenthouse oxygen tent; 12 x 12 x 10 inch).

100% oxygen (15 lpm) is blended with a NO/nitrogen mixture (800 ppm NO; balance N2) to yield a final concentration of 24 ppm NO, NO2 0.25 ppm, 97 % oxygen, 3 % nitrogen. This becomes the flow into the inner hood, from which the neonate breathes.

A suction apparatus is attached to the outer hood which suctions the gases in the outer hood at approximately 4 lpm. The NO/NO2 sensor lead in the inner hood also suctions approximately 4 lpm. Both suction systems are attached to a vented connector attached to the wall suction which entrains room air and is regulated to a negative pressure of –9 to –10 cm H20.

The concentration of NO in the inner hood with this apparatus is approximately 20 ppm, with NO2 0.95 ppm, and 97 % oxygen. The concentrations in the outer hood are: NO 15-17 ppm, with NO2 0.60-1.05 ppm, and 65-77 % oxygen.

On the outer surface of the hood, near the opening, the concentrations of NO are 0.45-0.55 ppm, with NO2 0.00 ppm, and 22-35 % oxygen. Further away from the hood, the oxygen concentration is 21% (same as room air) and NO2 is undetectable (0.00 ppm). NO levels are < 0.25 ppm at more than 12 inches (30 cm) from the hood.

Protocols:

After entry criteria are met, informed consent is obtained from the parents by either the study coordinator, research nurse, or attending physician/fellow and the neonate will be randomized to either the NO group or control group. The treatment gas will be administered by hood, with the clinicians and nurses blinded to assignment. The apparatus setup at the bedside would be identical for both groups and the NO flowmeter and NO/NO2 concentrations will be masked. FiO2 and NO/NO2 concentrations of the inflow gas will be monitored at the beginning of the study period and the sensors will then be moved to the inner hood. Respiratory therapists will adjust flow and blending to administer 20 ppm of NO or an equivalent flow of O2. FiO2 and NO/NO2 concentrations in the inner hood will be monitored continuously for the study period. Physicians and nurses caring for the patient and analyzing results will be blinded to patient assignment. After completion of one hour on the study, the gas will be weaned every hour over the next four hours (20 ppm at 1 hour to 10 ppm at 2 hours to 5 ppm at 3 hours to 2.5 ppm to 4 hours to 0 ppm at 5 hours), then discontinued. If marked deterioration (decrease in oxygen saturation of > 5%) is seen during the weaning phase, the treatment gas can be increased to the previous level and can then be weaned subsequently by the same decrement but over two hours. The attending physician can initiate mechanical ventilation at any point during this study, based on clinical or other grounds. If methemoglobinemia (MetHb>5%) occurs, or if NO2 concentrations are >3% in the inner hood, or if oxygenation decreases significantly (decrease in oxygen saturation of > 5%), or if other adverse reactions that could possibly be related temporally to the treatment gas are evident, the gas is to be weaned in a shorter timespan (50% every 15 minutes). The results of these neonates will still be analyzed based on "intention to treat". If at the end of the study period the infant still meets entry criteria, he/she will be crossed over into the other treatment group.

Monitoring:

1. Apparatus: FiO2 and NO/NO2 concentrations will be checked in the **inflow gas** at the beginning, and continuous monitoring of FiO2 and NO/NO2 concentrations in the **inner hood** will be done till exit from study. FiO2 and NO/NO2 concentrations will also be measured **outside the hood** 30 min and one hour after commencement of the treatment, at a distance of one foot (30 cm) from the front of the hood.
2. Baby: **ABGs** at 0 hours (the last ABG before beginning treatment gas) and 1 hour will be used for the study. **MetHb** will also be measured in these samples. Frequency of ABG and other lab investigations at other times will be at the discretion of the attending physician, but should be at least q 1 hour for the five hours on the study. **Oxygen saturation, heart rate, respiratory rate** and **blood pressures** (by arterial catheter) will be monitored continuously through the period of study. A **platelet count** obtained less than 12 hours before entry into the study will also be compared with one obtained immediately after completion of one hour of exposure to the treatment gas. **Echocardiograms** are encouraged before entry into the study, as echocardiograms are usually part of the clinical investigation in neonates with suspected PPHN, but are not a pre-requisite for entry in view of time and technical constraints.

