3.7 Study exit criteria

1. Completion of one hour on treatment gas followed by weaning to 100% oxygen by hood. If at the end of the study period the infant still meets entry criteria (A-a DO2 500- 600 mm Hg), he/she will be crossed over into the other treatment group.
2. If methemoglobinemia (MetHb>5%) occurs, or if NO2 concentrations are >3% in the inner hood, or if oxygenation decreases significantly (decrease in oxygen saturation of > 5%), or if other significant adverse reactions that could possibly be related temporally to the treatment gas are evident, the gas is to be weaned in a shorter timespan (50% every 15 minutes).
3. Sudden marked deterioration in any physiological variable, that in the opinion of the attending physician, requires initiation of mechanical ventilation or ECMO (initiation of inotropic support, change of intravenous fluid intake, or antibiotic therapy are not included in exit criteria).
4. Transfer to another institution / death / withdrawal from study by parent or attending physician

The study coordinator is to be contacted in cases where criteria 2, 3, or 4 are being considered.

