**4. Ethical considerations**

1. Is NO safe to administer by oxyhood? : 20 ppm of NO has been safely administered during mechanical ventilation to many neonates and infants over the last few years. Administration by oxygen hood, when the concentration of inhaled NO is being continuously monitored, is probably as safe or even safer than administration during mechanical ventilation, since the additional hazards of barotrauma/volutrauma of mechanical ventilation are not superimposed.
2. Is it ethical to withdraw NO after a one hour administration at 20 ppm? : Since this is a pilot study to evaluate the physiologic efficacy of the method, and is not an evaluation of long-term NO by oxyhood on clincal outcomes, it is ethical to wean off NO to 100% oxygen by hood, which is the established practice.
3. Is it ethical to use oxygen rather than nitrogen as the control gas, since the FiO2 of the oxygen group will be higher? : Oxygen is the established and conventional method, and is known to reduce pulmonary arterial pressures. Hence it is ethical to use oxygen rather than nitrogen as the control gas.
4. If weaning from treatment gas is difficult, should treatment be continued on a long term basis? : Again, since this study is to evaluate the physiologic efficacy and not clinical outcomes, and this method of administration is still experimental, we do not favor administration of the treatment gas on a long term basis, although slower weaning can be performed.
5. If a response is seen to the treatment gas, but is not marked, should the treatment gas concentration be increased?: No, most studies have shown that neonates who respond usually do so with 20 ppm. Also, with increasing treatment gas, FiO2 decreases. When the concentration is maintained at 20 ppm or less, FiO2 is more than 95%.
6. Is it ethical to use a control group, since NO is already known to reduce pulmonary pressures and improve oxygenation in mechanically ventilated animals and neonates? : Oxygen is the established and conventional method, and the administration of NO by hood is still experimental. Also, there is provision for a crossover to the other group if the neonate still meets entry criteria after weaning from the treatment gas, so in case of no improvement, the neonate will still access both forms of therapy.
7. **Feasibility**
   1. Available population / estimated recruitment time

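### During weaning, one event (a saturation fall of more than 5%) both permits a step back up and directs a faster wean, with no stated precedence

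*Protocol*

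**What the plan says.** Section 3.4 (Protocols) plans 20 ppm for the first hour, then 10, 5, 2.5 and 0 ppm at hours 2, 3, 4 and 5. Two rules for desaturation follow.

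- **Step back up.** "decrease in oxygen saturation of > 5%) is seen during the weaning phase, the treatment gas can be increased to the previous level". The same decrement is then made over two hours.
- **Faster wean.** A list of triggers (methemoglobin, NO2, a saturation fall of more than 5%, other reactions) ends in one instruction: "the gas is to be weaned in a shorter timespan (50% every 15 minutes". No phase is named.

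Section 3.7 item 2 restates the second rule among the exit criteria, with the trigger "if oxygenation decreases significantly (decrease in oxygen saturation of > 5"%. It sets no phase limit and does not mention the step back up. The section closes: "The study coordinator is to be contacted in cases where criteria 2, 3, or 4 are being considered".

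Section 4 item 4, on difficult weaning, declines long-term treatment, "although slower weaning can be performed". Section 3.4 also states: "The attending physician can initiate mechanical ventilation at any point during this study, based on clinical or other grounds".

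**The concern.** A fall of more than 5% between hours 1 and 5, while gas is still flowing, meets both triggers. One rule raises the dose and slows the wean; the other cuts the dose and speeds it. The first is optional and the second is directed, so a literal reader would follow the second. That is the less plausible intent, because an infant who desaturates as nitric oxide is reduced may be reacting to the reduction. The event is foreseeable: the protocol wrote a rule for it, and the Summary (Study measurements) calls for assessment of rebound in oxygenation.

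At stake are infant safety during weaning, time on gas, whether the fall counts as an exit event, and when the period ends and crossover eligibility is judged. The dose consequence is confined to infants receiving nitric oxide. For infants on oxygen, only the schedule and the exit status differ.

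**Working it through.** **Step 1: compare the rules.**

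| | Step back up (3.4) | Faster wean (3.4) | Exit item 2 (3.7) |
|---|---|---|---|
| Saturation trigger | fall > 5% | fall > 5% | fall > 5% |
| Phase | weaning | none stated | none stated |
| Force | optional | directed | directed |
| Action | previous level, then same step over 2 h | 50% every 15 min | 50% every 15 min |
| Refers to the other rule | no | no | no |

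Threshold and event are identical, the actions are opposite, and neither rule defers to the other. A fall after the gas has reached 0 ppm creates no conflict, because there is nothing left to wean faster.

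**Step 2: look for a tie-breaker.** Three cues favour the step back up:

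- It is the rule specific to weaning.
- The faster-wean list ends "or if other adverse reactions that could possibly be related temporally to the treatment gas are evident", which groups the fall with reactions to the gas rather than to its removal.
- Section 4 item 4 allows slower weaning.

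None of the three says that the directive is suspended during weaning.

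**Step 3: size the gap between the instructions.** The inputs are the Section 3.4 schedule and the two wean rates. The assumptions are an infant on nitric oxide, a fall seen as the level is reached, first halving 15 minutes later, a last step from 2.5 to 0 ppm as planned, and no second fall. Let t be the hour of the fall and k the number of planned steps left to 0 ppm (k = 3, 2, 1).

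- Step back up, only the repeated step slowed: end = t + 2 + k
- Step back up, every later step also slowed: end = t + 2(k + 1)
- Faster wean: end = t + 0.25k

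| Level at fall (hour t) | ppm 15 min later: step up / faster wean | End, step up | End, step up, longer reading | End, faster wean | Difference (longer reading) |
|---|---|---|---|---|---|
| 10 ppm (2) | 20 / 5 | 2+2+3 = 7 | 2+8 = 10 | 2.75 | 4.25 h (7.25 h) |
| 5 ppm (3) | 10 / 2.5 | 3+2+2 = 7 | 3+6 = 9 | 3.5 | 3.5 h (5.5 h) |
| 2.5 ppm (4) | 5 / 0 | 4+2+1 = 7 | 4+4 = 8 | 4.25 | 2.75 h (3.75 h) |

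If halving continued below 2.5 ppm, the last 15-minute dose would be 1.25 rather than 0 ppm. The next step down takes 120 minutes under one rule and 15 under the other (120/15 = 8 times). The planned end is hour 5, so the step back up adds 2 hours on the shorter reading, and the faster wean removes 2.25, 1.5 or 0.75 hours.

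**Step 4: check the primary outcome.** It is PaO2 after one hour of gas. Weaning starts after that hour, so the first-period value is already fixed. Section 3.4 keeps infants weaned faster in the intention-to-treat analysis.

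**The case against.** The strongest reply is that the document, read as a whole, already resolves the matter. A rule written for weaning governs weaning, the general rule sits in a list of harms from the gas, and Section 4 item 4 points to slower weaning. Section 3.7 is an exit list, and the bedside procedure is in Section 3.4. On this view only a cross-reference is missing. This has weight: the text leans toward the safer reading. But the two rules stand in the same paragraph of Section 3.4, so the conflict does not depend on reading Section 3.7 alone, and an optional rule does not override a directed one without saying so.

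A second reply is that there are backstops. The coordinator must be contacted when exit item 2 is considered and, because the coordinator assigns infants from the envelopes (Section 3.3), may know the arm. The attending physician may ventilate at any time. Both help, but neither supplies a rule for the gas.

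Three stronger readings are tempting and are not supported.

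- **Blinding makes the choice impossible.** Section 3.4 does say "Physicians and nurses caring for the patient and analyzing results will be blinded to patient assignment", but elapsed time identifies the phase, and a rule set by phase needs no knowledge of the arm. Blinding adds little.
- **The hour figures measure harm.** They measure the distance between two schedules, on stated assumptions. They apply only if staff take the reading that is probably not intended.
- **The trial's main result is compromised.** The first-period primary outcome precedes weaning, and no power or error-rate question arises.

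**Conclusion.** The point holds as a contradiction between stated rules with a safety consequence; the fault is in what the protocol says, so it is more than missing detail. During weaning, the same fall permits a return to the previous level and directs halving every 15 minutes. The probable intent is the step back up, but no text says so.

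If the literal directive were followed in an infant on nitric oxide, the dose 15 minutes later would be a quarter of the stepped-up dose at the 10 and 5 ppm levels (5 against 20, 2.5 against 10), and 0 against 5 ppm at the last level. The gas would end 2.75 to 4.25 hours sooner than under the step back up, or 3.75 to 7.25 hours sooner if every later step is slowed. These figures rest on the assumptions in the working. The protocol gives no rate of such falls, so the number of infants affected cannot be estimated. The overlap in wording is certain; the practical harm is not. It should be corrected because the remedy costs almost nothing.

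**What to change.** Make the same change in Sections 3.4 and 3.7:

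- State that a saturation fall of more than 5% during weaning is handled first by returning to the previous level and re-weaning that step over two hours, and that it is not in itself an exit event.
- Apply the desaturation trigger for the faster wean in two situations: a fall during the initial 20 ppm hour, and a fall that persists after the gas has been returned to the previous level. Both are needed, because limiting the trigger to the 20 ppm hour would leave a persistent fall without a rule. The investigators should state on clinical grounds how long counts as persisting; the protocol gives no figure.
- Keep the methemoglobin, NO2 and other adverse-reaction triggers in force throughout.

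This agrees with Section 4 item 4 and can be followed without unblinding. The cost is wording in two places, with no extra infants or samples and no loss of power.

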
The majority of the available literature as briefly described above deals with neonates on mechanical ventilation, since NO has been used so far as a “rescue” therapy for infants not responding to conventional, and in some cases, high frequency ventilation. Kakuya et al. (12) reported on the use of inhaled NO via a nasopharyngeal tube in an infant with a severely hypoplastic lung and end-stage pulmonary hypertension. Clinical improvement was maintained for seven days with 18-22 ppm NO inhalation. Environmental NO levels were less than 0.06 ppm and NO2 < 0.3 ppm throughout the treatment, well within safety margins. The use of a nasopharyngeal NO delivery system without sedation, as an alternative to endotracheal intubation and sedation, was thought to be advantageous and a practical method in this situation for maintaining a certain quality of life for the patient and family. However, due to entrainment of room air with varying patterns of respiration and varying contributions from mouth breathing, the actual delivered NO level by this method cannot be ascertained with accuracy. The other problem with this method is that the presence of a nasal catheter will partially or even completely occlude one nostril and increase airway resistance significantly (possibly by up to 50%) (13,14), further compromising respiratory effort and oxygenation in a neonate with abnormal gas exchange. NO has also been delivered by a pulsed nasal cannula in older infants and children and shown to decrease pulmonary arterial pressures and resistance as effectively as NO delivered by face mask (15). However, this method has the same flaws as delivery with a nasopharyngeal cannula (12).

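### The inner-hood NO2 limit that triggers the accelerated wean is written as 3% (30,000 ppm), which an 800 ppm NO source cannot produce; the unit should almost certainly be ppm.

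*Protocol*

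**What the plan says.** Section 3.4 (Protocols) lists the events that shorten the wean to a 50% reduction every 15 minutes: methaemoglobin above 5%, a fall in saturation of more than 5%, other adverse reactions possibly related to the gas, and an NO2 limit, "if NO2 concentrations are >3% in the inner hood". Section 3.7, item 2, repeats the limit in the same unit: "or if NO2 concentrations are >3% in the inner hood".

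Every other NO2 concentration in the protocol is in ppm. Section 3.4 (Apparatus) describes the inner hood in normal operation as NO at "approximately 20 ppm, with NO2 0.95 ppm, and 97 % oxygen". The supply is a single NO-in-nitrogen source at 800 ppm, blended with 15 lpm of oxygen to give 24 ppm NO and 0.25 ppm NO2 at inflow. The case report in section 2.2 also uses ppm: "Environmental NO levels were less than 0.06 ppm and NO2 < 0.3 ppm throughout the treatment".

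Section 3.4 (Monitoring, item 1) calls for "continuous monitoring of FiO2 and NO/NO2 concentrations in the" inner hood. The same section says of the bedside set-up that "the NO flowmeter and NO/NO2 concentrations will be masked", and that physicians and nurses are blinded.

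**The concern.** A percentage is the wrong scale for NO2 in this apparatus. Taken literally, the limit lies far above anything the gas supply can generate, so the NO2 part of the rule could never be met. No other section gives an inner-hood NO2 limit in ppm that would override it.

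The consequence concerns safety conduct. The other parts of the rule respond to an effect already seen in the infant, whereas the NO2 limit is the part meant to act on exposure itself. Because the readings are masked at the bedside, a usable written number is what would turn an NO2 reading into action. Section 3.7 also asks for the study coordinator to be contacted when item 2 is being considered, and a limit that cannot be reached would not prompt that contact either.

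**Working it through.** **Inputs** (section 3.4 unless stated)

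- NO2 limit: above 3% (also section 3.7, item 2)
- NO source: 800 ppm; oxygen flow: 15 lpm
- Inflow gas: 24 ppm NO, 0.25 ppm NO2, 97% oxygen, 3% nitrogen
- Inner hood in normal use: about 20 ppm NO, 0.95 ppm NO2
- Wean: 20, 10, 5 and 2.5 ppm at 1, 2, 3 and 4 hours on schedule; 50% every 15 minutes if accelerated

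**Step 1. Reproduce the stated blend.** With source flow f, 800 × f / (15 + f) = 24 gives f = 24 × 15 / (800 − 24) = 0.464 lpm. Oxygen is then 15 / 15.464 = 97.0% and nitrogen about 3.0%. Both match the protocol, so its ppm figures for the supply are coherent.

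**Step 2. Literal reading.** 3% × 1,000,000 = 30,000 ppm. One NO molecule yields at most one NO2 molecule, which bounds the NO2 that can form:

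| Gas | Most NO2 possible or stated | 30,000 ppm divided by it |
|---|---|---|
| Undiluted source, fully oxidised | 800 ppm (0.08%) | 37.5 |
| Blended inflow, fully oxidised | 24 + 0.25 = 24.25 ppm | about 1,237 |
| Inner hood, normal use | 0.95 ppm (stated) | about 31,600 |

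The limit cannot be reached under any failure of dilution or any degree of oxidation.

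**Step 3. Percentage as a share of NO.** 0.03 × 20 = 0.6 ppm in the inner hood, or 0.03 × 24 = 0.72 ppm on the inflow concentration. Both are below the normal 0.95 ppm, which is 0.95 / 20 = 4.75% of the NO level. On this reading the rule would fire during routine delivery at 20 ppm.

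**Step 4. Unit read as ppm.** 3 / 0.95 = 3.2 times the normal level. Reaching it needs 3 / 24.25 = 12% of the inflow NO and NO2 to be present as NO2. Of the three readings, only this one is both reachable and above normal operation.

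**Step 5. What the trigger changes.** From 20 to 2.5 ppm is three halvings. On schedule they take 3 × 1 h = 3 h; accelerated, 3 × 15 min = 45 min. This comparison starts at the end of the first hour. For a high reading during the 20 ppm hour, the rest of that hour would be added to the scheduled path.

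**The case against.** The strongest reply is that the slip nearly corrects itself. All other NO2 values are in ppm, and an operator comparing a ppm reading with a limit of 3 is unlikely to think 30,000 ppm was meant. The more absurd the literal value, the less likely anyone is to apply it, so the 31,600-fold ratio measures implausibility and not risk. The masking is also partial: respiratory therapists adjust the blend to reach 20 ppm, so they very likely see the analyser, and they are not named among the blinded staff. The attending physician may start ventilation or withdraw the infant at any time, and three other parts of the rule still work. The contrast between 3 hours and 45 minutes matters only if NO2 is high while none of those other parts is met.

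Much of this stands, and it limits the probable harm. It cannot be said that an infant would be left on the gas, only that this follows if the rule is applied as written and nobody queries it. The reply does not make the limit correct. It relies on staff replacing the written unit with one the protocol never gives for this limit. A therapist who sees the reading still needs a valid number to act on.

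**Conclusion.** The concern holds. The NO2 limit is wrong as written in both places where it appears: 30,000 ppm is 37.5 times the NO content of the undiluted source, and reading it as a share of the NO level gives a limit below normal operation. The only NO2-specific action rule is therefore inoperative on its literal wording.

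The unreachability rests on the 800 ppm cylinder being the only NO source and on conservation of nitrogen. The failure of the share reading rests on the stated 0.95 ppm. That ppm was intended is an inference, though a strong one.

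The error is confined to safety conduct. Sample size, power, eligibility and the primary analysis are untouched, and nothing in the protocol suggests that hazardous NO2 is expected. It should still be corrected before use, because it is a numeric safety limit for neonates.

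**What to change.** In section 3.4 (Protocols) and section 3.7, item 2, replace the percentage with a limit in ppm and have the investigators confirm the value. If 3 ppm was meant, both places should state that the accelerated wean starts when inner-hood NO2 exceeds 3 ppm. It would help to add that the respiratory therapist, or another unmasked person reading the analyser, is responsible for acting on it.

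The change is a wording correction in two places. It costs no patients, no power and no change to the design.
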